## 1. INTRODUCTION AND RATIONALE

### *NAFLD: a significant liver disease*

The prevalence and severity of NAFLD - excessive hepatic fat accumulation without excessive alcohol consumption – are increasing at an alarming rate, because more and more patients are living longer with the two main factors that drive NAFLD: obesity and T2DM. 20-30% of the global population including The Netherlands has some stage of NAFLD, and in patients with T2DM, this is even as high as 60-80%. NAFLD is regarded as the hepatic component of the metabolic syndrome (MetSy) and T2DM. It can silently progress from simple steatosis to NASH (prevalence 2-3%) and NASH-related fibrosis, and ultimately to cirrhosis and hepatocellular carcinoma (fig.1).

[figure not shown]

Figure 1. The disease spectrum of NAFLD

[figure not shown]

**Figure 2. The pathogenesis of NAFLD-NASH.** NAFLD-NASH has a complex pathogenesis with a multiplicity of pathways. Yet centrally stands insulin resistance, causing lipolysis in peripheral adipose tissue, resulting in increased hepatopetal free fatty acid (FFA) flux. These FFAs are stored as triglycerides in hepatic lipid droplets. This in turn reduces hepatic insulin sensitivity, increasing hepatic gluconeogenesis and glucose secretion contributing to hyperglycemia, but also to subsequent intrahepatic conversion of glucose to even more lipids. Systemic insulin resistance amplifies this process, since high plasma insulin and glucose upregulate Sterol Regulatory Element-Binding transcription factor 1c and Carbohydrate-Responsive Element-Binding Protein signaling, further stimulating lipogenesis. This drives hepatic lipotoxicity, triggering NASH, necroinflammation and activation of hepatic stellate cells, initiating fibrogenesis.

From Ruissen, [name], European Journal of Endocrinology 2020

Progression into the fibrotic stages of NAFLD is strongly associated with liver-related and overall mortality and increased risk of atherosclerotic cardiovascular disease, the latter most likely via induction of dyslipidemia. Although NAFLD-NASH has a complex pathogenesis with a multiplicity of pathways, it is thought that insulin resistance is a crucial trigger since it causes lipolysis in peripheral adipose tissue, resulting in increased hepatopetal free fatty acid (FFA) flux. This drives hepatic lipotoxicity, triggering NASH, necroinflammation and activation of hepatic stellate cells, initiating fibrogenesis. (for detail, see figure 2).

### *NAFLD: paucity of treatments and the potential of the gut microbiome*

To date, no treatment is available for progressive NAFLD stages. However, based on insights from observational studies and animal experiments, the gut microbiome and its metabolites are emerging as an innovative approach to treat this challenging metabolic liver disease. Potentially detrimental alterations in gut microbial composition have frequently been observed in NAFLD: aberrant microbiota composition, often depleted in butyrate producers, reduced diversity, small intestinal bacterial overgrowth and signs of increased gut permeability. This project aims to study the effects of the combination of bacterial strains on NAFLD.

### *Anaerobutyricum soehngenii*

We recently published the first vegan fecal microbiota transplantation study in patients with NASH and aberrant microbial composition. This pilot study found anti-inflammatory effects of vegan FMT into NASH patients, with a trend towards reduced hepatic necro-inflammation (fig.3). Upon vegan FMT engraftment, the gut microbiome of the NASH patients was enriched in *Anaerobutyricum soehngenii* (also/formerly known as *Eubacterium hallii*) and other butyrate-producing Lachnospiraceae (fig.4). Furthermore, in obese mice, *A. soehngenii* treatment improved insulin sensitivity and reduced intrahepatic triglyceride content. Of note, *A. soehngenii* is well known to not only convert sugars but also lactate and acetate into butyrate, a short chain fatty acid that may protect against NASH. Butyrate may reduce the inflammatory component of NAFLD by promoting differentiation of regulatory T cells. It also has an anti-migratory effects on neutrophils, and in the gut, it protects epithelial barrier integrity, both potentially protective effects on NASH. Moreover, since lactate is found to be increased in T2DM; the efficient conversion of lactate into butyrate by *A. soehngenii* is expected to contribute to its beneficial actions.

### *Bifidobacterium.animalis* subsp. *lactis*

Another species thought to be beneficial is *B.animalis* subsp. *lactis* of which the well-studied strain BLC1 is marketed as a probiotic and well characterized. In vitro studies have shown that this strain can form a trophic chain with *A. soehngenii* to accelerate butyrate production from FOS. In addition, the BLC1 strain can in conjunction with *A. soehngenii* improve butyrate production in a model of the small intestine (Deyaert et al 2022, in preparation). Moreover, *B.animalis* subsp *lactis* with FOS has been shown to improve intestinal discomfort and promote anti-inflammatory properties.

[figure not shown]

Figure 3. Changes in necro-inflammation score of liver histology following either autologous (i.e. from the patients with NASH, ergo control; red) or allogenic (i.e. from vegan donors; blue) FMT in patients with NASH. From Witjes et al, Hepatology Communications 2020.

[figure not shown]

Figure 4. Radar plots of significantly altered fecal microbial strains following either autologous (red) or allogenic (blue) vegan FMT. Grey arrows indicate higher *E. hallii* species (now known as *A. soehngenii*). From Witjes et al, Hepatology Communications 2020.

### *Akkermansia muciniphila*

Pasteurized *A. muciniphila* is involved in host immunological homeostasis at the gut mucosa, improvement of gut barrier function and contributes to metabolic health. Indeed, in a study assessing the effects of pasteurized *A. muciniphila* on diet-induced metabolic disorders in mice, it was not only found that pasteurization did not diminish the beneficial effects, but it also unexpectedly enhanced the beneficial impact of *A. muciniphila* on insulin resistance and dyslipidemia. Also, *A. muciniphila* and *A. soehngenii* work in a bidirectional syntrophy. *A. soehngenii* produces butyrate and pseudovitamin B12. Pseudovitamin B12, in turn, stimulates *A. muciniphila* to convert of acetate into propionate, thereby stimulating *A. soehngenii* to its production of butyrate and pseudovitamin B12. In addition, a randomized, double-blind, placebo-controlled proof-of-concept study in overweight/obese insulin-resistant human volunteers showed that the daily supplementation with pasteurized *A. muciniphila* at a daily

dose of  $10^{10}$  cells (based upon CFU count) for 12 weeks improved several metabolic parameters such as insulin sensitivity, insulinemia, plasma total cholesterol, as well as relevant blood markers for liver dysfunction and inflammation while serum lipopolysaccharide (LPS) levels were decreased, indicative of improved barrier function. A recent study in a high fat induced fatty liver mouse model showed that administration of *A. muciniphila* cells prevented fatty liver disease by regulation of the expression of genes that regulate fat synthesis and inflammation in the liver. Since these studies all found that pasteurized *A. muciniphila* cells were similar or more efficient than the same amount of live *A. muciniphila* cells, we aim to use pasteurized *A. muciniphila* ATCC BAA-835T cells in the present study. Of importance, these cells have recently received EFSA approval based on the extensive toxicological safety assessment.

#### *The used probiotic bacteria may reduce NAFLD via glucagon-like peptide 1*

Recently studies found an interesting mechanism by which *A. soehngenii* may reduce NASH. In patients with MetSy, of which NAFLD is considered the hepatic equivalent, duodenal administration of *A. soehngenii* strongly increased glucagon-like peptide 1 (GLP1) secretion from the enteric endocrine L-cells, potentially relating to the observed reduced plasma glucose fluctuations (fig.5). Of note, *A. muciniphila* administration induced GLP1 secretion in a mouse model. Interestingly, clinical evidence is mounting that enhancing GLP1 may be a plausible approach to reduce NASH. In a subset of patients from the phase 2A LEAN trial with a GLP1-receptor agonist, it was shown that in addition to weight loss and improved glycemic control, insulin-resistance driven hepatopetal FFA-flux – the main contributor to lipid overload in NAFLD - was reduced. In a recent Ph2B trial with a next generation GLP1 receptor agonist, NASH histology improved and signs of fibrosis regression were noted. Thus among the aims of our studies is the explore the effects of the combined bacterial strains on GLP1 secretion.

#### *Combination therapy may be required to treat NAFLD; the potential of synbiotic treatment*

Yet of note, in larger phase 3 designs, some other single-drug studies have recently reported futility for NASH. It is therefore quite broadly anticipated by both experts in the field as well as pharmaceutical companies that combination therapy may be more effective for NASH, as it is for other elements of MetSy such as T2DM, hypertension and dyslipidemia.

[figure not shown]

Figure 5. Duodenal *A. soehngenii* infusion in 12 patients with metabolic syndrome. Left panel: increased plasma GLP1 during mixed-meal test; right panel: median absolute deviation of continuous glucose measurements over the first 24 hours after placebo/treatment intervention. From Koopen et al, Gut 2021

This notion may also hold true when aiming to tap into the therapeutic potential of the gut microbiome for NASH. In particular, candidate therapeutic bacteria may be potentiated when combined with prebiotics, i.e. non-digestible food substances, which can be fermented by bacteria, promoting their growth. Such combinations are termed synbiotics. Early evidence from murine studies and pilot studies with synbiotic cocktails in NASH patients underscore the feasibility of this approach. NASH-fibrosis was reduced by a cocktail of 4 prebiotics and 4 probiotics in a high fat- choline-deficient diet mouse model. In addition, ALT and TNF $\alpha$  were reduced in patients with NAFLD who received a synbiotic cocktail of 7 bacterial strains with the prebiotic fructo-oligosaccharides (FOS; oligomer of <10 fructose molecules). In another pilot study in patients with NASH, a 12-week treatment with a synbiotic cocktail of 5 probiotic bacteria and fructo-oligosaccharides reduced ALT and liver stiffness on elastography. Together these reports are supportive, yet the murine study did not decipher any mechanisms underlying the protective effects and the human studies e.g. did not provide liver histology, the gold standard in therapeutic development for NASH.

Furthermore, FOS is degraded to lactate and acetate by *Bifidobacteria* spp. such as *Bifidobacterium longum* or *B. animalis* subsp. *lactis*, a well-studied strain applied as a probiotic. The generated lactate and acetate has shown to be effectively converted by *A. soehngenii* into butyrate in *in vitro* experiments, including simulated ileum and colon models at ProDigest (Deyaert et al 2022, manuscript in preparation). Such a cross-feeding mechanism can play a role in the colon ecosystem and contribute to the combined bifidogenic/butyrogenic effect observed after addition of FOS to the diet. In this context a recent human intervention study should be noted where administration of *B. animalis* subsp. *lactis* with FOS was found to improve intestinal discomfort and promote anti-inflammatory properties.

In our study, we will apply the complementary mode of actions of the individual components in the synbiotic treatment, the established effects of their combinations, and their expected impact on both upper intestinal tract and colon. We hypothesize that for NASH, synbiotic combination treatment will change the tipping point in the gut microbiome in order to reduce steatohepatitis and liver fibrosis.

## 2. OBJECTIVES

### Primary objective

To investigate the therapeutic potential of *A. soehngenii* and pasteurized *A. muciniphila* combined with *B. animalis* subsp. *lactis* and FOS with and without conditioned vegan Lyophilized fecal microbiota transplantation (LFMT) capsules to reduce NASH in patients with fibrotic NASH.

### Secondary objective

To investigate the mechanisms of *A. soehngenii* and pasteurized *A. muciniphila* combined with *B. animalis* subsp. *lactis* and FOS with and without conditioned vegan LFMT capsules in reducing NASH in patients with fibrotic NASH.

## 3. STUDY DESIGN

### Study visits:

Participants who are foreseen to fulfil the inclusion / exclusion criteria for enrolment into the clinical study will be informed and interviewed. When theoretically eligible for participation, participants are asked to give informed consent in writing prior to any clinical study specific procedures. Both the participant and investigator (or designee) will sign and date the informed consent form. After, a liver biopsy will be performed (unless there is a liver biopsy available obtained < 32 weeks prior to screening) to assess if histopathological inclusion criteria are met.

A MRI of the liver and surrounding area (including pancreas and visceral adipose tissue; as previously specified) will be performed for all eligible participants before the biopsy, unless the biopsy was already performed prior to inclusion.

All eligible participants will visit the study physician 4 times; at baseline, after 8, 16, and 24 week. The study visits will be 8 weeks apart, although a margin of -3 days to +3 days is implemented to take participants schedule and availability into account.. At baseline, blood

and feces, will be collected, a Fibroscan will be made and participants will fill out the SF36.2 and CDLQ-NAFLD quality of life questionnaires. After, participants receive 21 LFMT or placebo capsules to orally ingest. The ingestion of the 21 capsules will be spread over the day to prevent clotting of capsules in the stomach. In addition, for the whole duration of the study participants will daily ingest 2 LFMT capsules (or placebo). At the next visit after 8 weeks blood will be withdrawn, feces will be collected and patients will again ingest 21 LFMT capsules (or placebo). The visit at 16 weeks will be the same as the visit at 8 weeks. The visit at 24 week will be the same as the baseline visit, however, at 24 weeks the visit will also include a liver biopsy. Moreover, patients will hand in fecal samples at baseline, week 2, 8, 10, 16, 18, and 24. Also, continuous glucose measurements will be performed at home using portable devices, during a consecutive period of 1 week (7 days) in the week before baseline, week 1, 9, 17 and 25.

Throughout the study period, the participants will, in addition to the LFMT or placebo capsules, take the 3 bacterial strains in the morning combined with FOS. They will further be asked to retain their usual dietary habits during the study and to keep a nutritional diary from week -1 to 24 to monitor caloric intake including total calories, dietary carbohydrates, fat, proteins, and fibers. Blood pressure, body weight, and changes in health status will be documented.

Interventions: From the day of the first LFMT capsules until completion of the study, all participants will receive an oral daily dose of 5 grams of fructo-oligosaccharides [Sensus, Roosendaal]. Subsequently, participants will be randomized to receive lean donor LFMT or placebo capsules. This consists of 21 capsules at the first 3 study visits, and a daily ingestion of 2 capsules during the duration of the study (24 weeks). Placebo capsules will consist of saline with a brown pigment. During the 24 week study duration, all participants will also daily take  $10^9$  *A. soehngenii* CH-106 cells (dosage based on previous studies and safety study; provided by Caelus Health),  $10^{10}$  *B. animalis* subsp. *lactis* BLC1 (commercially available Sacco SRL) and  $3 \times 10^{10}$  pasteurized *A. muciniphila* cells (provided by A-Mansia Biotech), and 5 grams of FOS. We have previously observed that gut microbiota composition in the recipient is affected up to 8-12 weeks after donor FMT, so this time window ensures a stable donor gut microbiota composition during the study. The fecal donor samples will be collected, lyophilized ('freeze-dried'), encapsulated and stored at -80°C (see also paragraph 6.8). At home, participants will store the LFMT capsules in the freezer (-20°C). See figure 6 below.

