## SYNCH trial

|               |                                                                                                                                     |
|---------------|-------------------------------------------------------------------------------------------------------------------------------------|
| Participants: | 18 – 75 years with fibrotic NASH (NAS $\geq 3$ , NASH F1-F3 $\geq 50\%$ , F0 $\leq 50\%$ )                                          |
| Arm 1:        | n = 24 receive vegan LFMT-capsules + A. soehngenii , B. animalis subsp. lactis and A. muciniphila       |
| Arm 2:        | n = 24 receive placebo-capsules (saline) + A. soehngenii , B. animalis subsp. lactis and A. muciniphila |

[figure not shown]

Figure 6: Study protocol

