## **6.2 Name and description of investigational product(s)**

Participants will be treated with either allogenic LFMT capsules of a vegan donor or capsules with saline placebo with brown pigment (NaCl 0.9%). Stool of lean vegan donors is collected, lyophilized (freeze-dried), encapsulated in NGE capsules, and stored in  $-80^{\circ}\text{C}$  (see paragraph 6.8). The day prior to the first study visit, participants will ingest laxatives (macrogol/kleanprep) to enhance engraftment. At the study visits at baseline, week 8 and 16, participants ingest 21 LFMT-capsules. All other days of the 24 week study period, participants ingest 2 LFMT capsules.

Daily, participants will have to take one capsule of *Anaerobutyricum soehngenii* CH106 ( $\geq 1 \times 10^9$  live bacterial cells), one capsule of *Bifidobacterium animalis* subsp. Lactis BLC1 ( $\geq 1 \times 10^{10}$  live bacterial cells), one capsule of pasteurized *Akkermansia muciniphila* MucT ( $\geq 3 \times 10^{10}$  pasteurized bacterial cells), and 5 grams of fructo-oligosaccharides.

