### **6.7 Dosages, dosage modifications and method of administration**

#### *Allogenic Lyophilized Fecal Microbiota Transplantation (LFMT) capsules*

One LFMT capsule will contain approximately 235mg of lyophilized feces. This equals the bacterial load of approximately 750mg fresh feces, or 1500mg of fresh FMT. Depending on the fecal matrix and the water content, this might be slightly more or less. The dosage of the capsules will consist of 3 times a loading dose, and a maintenance dose. The loading dose will be 21 capsules on 1 day, ingested at the study visits. The maintenance dose will consist of the ingestion of 2 capsules daily for 24 weeks. The loading doses and the maintenance dose together equal the amount of 100 grams of fresh FMT administered every 8 weeks.

Capsules are to be ingested with a glass of water on an empty stomach in the morning, preferably an hour before breakfast (while still fasted). Patients store the LFMT capsules at home in a freezer, but can let the capsules warm to room temperature before ingestion.

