### **6.8 Preparation and labelling of Investigational Medicinal Product**

#### *Allogenic Lyophilized Fecal Microbiota Transplantation (LFMT) capsules*

Feces donors deliver their fresh feces cooled to the investigator at the AMC. The autologous feces are directly processed, whereby the feces are homogenized 1:1 with a lyoprotectant solution (10% trehalose and 5% maltodextrin in sterile saline, all pharmaceutical grade). Thereafter, the fecal suspension is filtered through double non-woven gauzes in a metal funnel (sterile) to remove any particulate matter. The resulting FMT is transferred to sterile flasks, 50 ml/flask, and frozen at  $-80^{\circ}\text{C}$ . Next, the flasks with frozen FMT are placed in the drying chamber of a freeze-dryer (Zirbus VaCo 2) and lyophilized during 48 hours. The resulting lyophilized FMT is subsequently transferred to a mortar, ground to a fine powder and mixed with lubricant (silicon dioxide, pharmaceutical grade) to improve the flowing properties of the powder. If necessary, filler is added to the powder mixture (microcrystalline cellulose, pharmaceutical grade) to reach the necessary volume for the number of capsules to be filled. Finally, the LFMT powder is encapsulated in capsules with stomach acid resistant properties (NGE-caps, Capsugel). LFMT capsules are filled in opaque HDPE 50 ml containers (DUMA Twist-off), 28 capsules per container. Containers are labelled according to GMP-annex 13 and stored in a freezer at  $-80^{\circ}\text{C}$ .

The image below shows a schematic overview of the preparation to the LFMT capsules.

[figure not shown]

Figure 7: Overview of the production of LFMT capsules.

The label of the LFMT capsules will contain:

- the name of the study: the SYNCH-trial
- the Participant Number
- the Sponsor name
- the investigators name and contact details
- For investigational use only
- LFM-capsules.
- Contains: Bevat freeze-dried feces, natriumchloride, trehalose, maltodextrin and colloidal silicium dioxide.
- the Batch Number and the Expiry Date
- Storage conditions: Store at room temperature (-20 to -4°C), in a dry place away from direct sunlight – Keep away from children
- Instructions for use: Consume two caps per day, 15 minutes before breakfast with a glass of water.
- Emergency Contact Number
- Amsterdam UMCs address.

All labels of the bacterial strains and the FOS will contain:

- the name of the study: the SYNCH-trial
- the Participant Number
- the Sponsor name

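### The placebo is described as pigmented saline and the active capsule as a freeze-dried powder, so at most their colour is matched and the participant blind is at risk

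*Protocol*

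**What the plan says.** The placebo fill is described three times, each time as saline. Section 3 (Interventions) states "Placebo capsules will consist of saline with a brown pigment". The arm table in the same section has arm 2 "receive placebo-capsules (saline"). Section 6.2 refers to "capsules with saline placebo with brown pigment (NaCl 0.9" per cent).

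The active fill is set out in section 6.8. It starts as a suspension in which "the feces are homogenized 1:1 with a lyoprotectant solution (10% trehalose and 5% maltodextrin in sterile saline, all pharmaceutical grade"). The suspension is filtered, frozen, lyophilized for 48 hours, then "ground to a fine powder and mixed with lubricant (silicon dioxide, pharmaceutical grade) to improve the flowing properties of the powder". The section adds "If necessary, filler is added to the powder mixture (microcrystalline cellulose, pharmaceutical grade"). The powder goes into NGE capsules. Section 6.7 gives about 235 mg per capsule, equated to 750 mg of fresh feces or 1500 mg of fresh FMT.

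Section 3 has participants keep the LFMT capsules in a freezer at -20°C, and section 6.7 says they "can let the capsules warm to room temperature before ingestion". Section 8.2 calls the trial double blind. No section gives the placebo a powder form, a fill weight, the NGE shell or the excipients of the active capsule.

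**The concern.** A brown pigment deals with colour only. A capsule placebo for a powder product should also match in form, weight and handling, and the protocol names a fill that is not of that kind. This is a stated composition, not a detail left to another document.

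If some participants form a view of their allocation, several things can shift before the week-24 biopsy:

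- **Diet.** Section 3 asks participants to keep their usual diet. A change in diet could affect metabolic and liver outcomes.
- **Adherence, withdrawal and replacement.** Under section 8.4.1, not following instructions or a change in prescribed drugs leads to withdrawal, and section 8.5 replaces those withdrawn. If guessed allocation influences who leaves, the set that reaches biopsy can differ between arms.
- **Adverse events.** Section 9.2.4 collects non-serious events only if they are possibly related to the study, and section 9.2.5 leaves that judgement to the investigator.
- **Quality of life.** The two questionnaires are self-reported.

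With 24 per arm, one participant is 1/24 = 4.2 percentage points of an arm's responder proportion, so a few affected participants would count.

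**Working it through.** No stated figure needs to be reproduced. The check compares the two fills under each possible reading of saline, then sizes the excipient difference.

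**Inputs.** Active fill about 235 mg; 750 mg feces and 1500 mg FMT per capsule (section 6.7). Lyoprotectant solution of 10% trehalose and 5% maltodextrin, mixed 1:1 with feces (section 6.8). Saline at 0.9% (section 6.2). Schedule of 21 capsules on three visit days and 2 daily for 24 weeks, which is 168 days.

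**1. Saline as a liquid.** This is the natural reading of a 0.9% solution, although the word liquid is not used. The form then differs from a dry powder, both frozen at home and after warming. The weights would agree only if each capsule were filled with about 0.235 mL (density about 1), and the protocol does not say so.

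**2. Saline that has been dried.** The volume is not stated, so assume 0.5 to 1.0 mL per capsule. At 9 mg NaCl per mL:

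- 0.5 mL × 9 = 4.5 mg
- 1.0 mL × 9 = 9 mg

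Against 235 mg, the active fill is 235/9 = 26 to 235/4.5 = 52 times heavier, before pigment. Reaching 235 mg from salt alone would take 235/9 = 26 mL of saline per capsule. No filler is named for the placebo.

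On either reading, the described placebo does not match the active fill in both form and mass.

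**3. Opportunity to notice.** If the daily pair is omitted on the three visit days, as section 6.2 implies: 3 × 21 + 2 × 165 = 393 capsules. If it is taken every day: 3 × 21 + 2 × 168 = 399.

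**4. Excipients.** The 1:1 mix agrees with section 6.7: 1500 − 750 = 750 mg of solution per capsule. Assume w/v percentages, density about 1, no filtration loss, and that 235 mg is the whole dried FMT.

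| Item | Calculation | Result |
|---|---|---|
| Trehalose | 750 × 0.10 | 75 mg |
| Maltodextrin | 750 × 0.05 | 37.5 mg |
| Sum per capsule | 75 + 37.5 | 112.5 mg |
| Share of fill | 112.5 / 235 | 48% |
| Maintenance day | 2 × 112.5 | 225 mg |
| Visit day | 21 × 112.5 | 2.36 g |

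The maintenance amount is 225/5000 = 4.5% of the 5 g FOS that both arms take daily. Maltodextrin and silica also reach both arms through the *A. soehngenii* capsule (sections 5.1 and 6.1.2), in amounts not given. Microcrystalline cellulose reaches both through the *A. muciniphila* capsule (section 6.1.2). Trehalose is the only excipient named for the LFMT capsule alone.

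**The case against.** A reader might infer that participants can tell the capsules apart, or that the placebo cannot keep them blind. The protocol does not support that. It does not give the opacity of the shell, the weight of the placebo or how either capsule feels. Allocation is parallel, so a participant receives one type and has no second capsule for comparison. The pigment shows that masking was intended. All of this stands, and it limits the point to a risk.

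The placebo descriptions are also short, section 6.8 covers only the LFMT capsule, and a product dossier may specify a matched placebo. That is possible and cannot be checked here. If it is so, the three statements in the protocol are wrong and still need correcting.

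The primary endpoint is histology, and the Summary has two pathologists blinded to any other result read the week-24 biopsy. Many secondary outcomes are imaging, laboratory or sequencing measures. This protects the reading of the slides. It does not protect behaviour or retention before the biopsy.

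A reader might further infer that the lyoprotectants confound the comparison of donor microbiota. The quantities do not show this: the daily amount is small beside the FOS, and the objective is to compare treatment with and without the LFMT product, of which the lyoprotectants are a part. The excipient difference is therefore a side point.

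**Conclusion.** The point holds as a design weakness worth correcting. As written, the placebo matches at most the colour of the active fill. It differs in form if the saline is liquid, and in mass by a factor of about 26 to 52 if it is dried, given an assumed volume of 0.5 to 1.0 mL. The double blind claimed in section 8.2 is thus not supported by the products described, and participant blinding is at risk over some 390 to 400 capsules each. Actual unblinding is not shown.

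The likely effect is on participant-driven outcomes and on who stays in the trial. It is indirect for the primary histology. The documents do not allow the size of any resulting bias to be estimated.

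**What to change.** In sections 3 (including the arm table), 6.2 and 6.8, replace the saline placebo with a brown-pigmented dry powder placebo. Microcrystalline cellulose and silicon dioxide are already on the excipient lists in sections 6.8 and 6.9. Adding trehalose and maltodextrin would also close the excipient gap and is preferable, though not essential for the blind. State that the placebo is filled to the same weight, in the same NGE shell and the same opaque container as the active capsule.

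The cost is modest. About 24 × 393 = 9,432 to 24 × 399 = 9,576 placebo capsules are needed whichever fill is used, and a cellulose-based powder needs no freeze-drying runs. There is some added production work, any saline placebo already made would be discarded, and the protocol must be amended. If capsules have already been dispensed, the report should state which placebo each participant received.
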